## 2. Background and rationale

The background and rationale for the trial are outlined in detail in the protocol. In brief, liver disease is the 5th largest cause of death in the UK, with mortality predicted to double in 20 years. Patients with liver disease die younger with the average age of death of 59 years, compared with 82-84 years for heart and lung disease and stroke. In England, in total 30,000–60,000 patients are at risk or affected by liver cirrhosis. One of the major complications of cirrhosis is portal hypertension and variceal bleeding. In patients with cirrhosis, varices develop at a rate of 5% per year with 10 year cumulative incidence of 44%. At least 3,000 patients are admitted to hospital in England per year with variceal bleeding, with inpatient mortality of 15% and one year mortality of up to 40%.

At present there are two options for primary prevention of variceal bleeding, namely non-selective beta-blockers and variceal band ligation. There have been two important guidelines published in the UK in 2015-2016 from NICE and the British Society of Gastroenterology (BSG). NICE favours banding for primary prevention, whereas the British Society of Gastroenterology (BSG) suggests banding if intolerant of beta-blockers. A large randomised controlled trial would help clinicians decide which the better treatment for primary prevention is as the current evidence is based on underpowered and low quality trials. Beta-blockers used for portal hypertension in the UK are propranolol and carvedilol. Carvedilol is better tolerated and therefore has been selected as the beta-blocker for this trial. If carvedilol is found to be superior to variceal band ligation then it will become first line therapy in primary prevention.

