### 9.3. Handling missing data

In the first instance, analysis will be completed on received data only with every effort made to follow-up participants even after protocol violation to minimise any potential for bias. For the primary outcome, a participant will be assumed to not have experienced variceal bleeding unless there is evidence to suggest otherwise. Therefore, there will be no missing data in this outcome for the primary analysis. However, sensitivity analysis will be performed on the primary outcome measure. See section 9.10 for further details.

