#### **Primary outcome measure**

The primary outcome measure for the comparison of carvedilol vs. variceal band ligation is variceal bleeding within 1 year of randomisation. We will define 1 year to be 365 days.

Variceal bleeding events are identified on the 6 month and 12 month follow-up forms. If a participant has at least one episode of variceal bleeding (including banding-related bleeding) indicated on either of these follow-up forms then they have “experienced variceal bleeding”. Participants which do not fulfil this criteria for experiencing variceal bleeding will be termed “free from variceal bleeding”.

For the primary outcome analysis, if a participant has “experienced variceal bleeding” and the date of onset of the first episode of bleeding as indicated on the follow-up form is within 365 days of the date of randomisation then the question “Has variceal bleeding occurred within 1 year of randomisation?” will be answered “yes”. Otherwise, it will be answered “no”. This will form the primary binary outcome.

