#### All-cause mortality at one year

Deaths are identified on the SAE form. If a participant has death indicated on an SAE form via the 'death' variable then they will be termed "dead". Participants which do not fulfil this criteria will be termed "alive".

If a participant is "dead" then their time till death will be defined as the number of days from the date of randomisation till the date death. If the time till death is  $\leq 365$  days then the question "All-cause mortality occurred by one year?" is termed "yes". If the time till death is  $> 365$  days then the question "All-cause mortality occurred by one year?" is termed "no".

If a participant is "alive" then their time till censoring will be the number of days from the date of randomisation to the date last known to be alive. This will be determined by the completion date of the most recent trial form received. If the censored time is  $> 365$  then the question "All-cause mortality occurred by one year?" is answered "no". If the censored time  $\leq 365$  days but the follow-up CRF has been completed within the window of assessment (no earlier than 351 days from randomisation) then "All-cause mortality occurred by one year?" is answered "no". If the censored time is  $\leq 365$  and the 12-month follow-up CRF has not been returned within the scheduled window of assessment then there is not complete information regarding mortality within 1 year for this participant. Therefore, the answer to "All-cause mortality occurred by one year?" is considered to be missing.

Liver-related mortality and cardiovascular mortality will be derived in a similar fashion. Deaths of these types will be classified and indicated on the database following review of the SAE information provided by the chief investigator.

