### **9.10. Sensitivity analyses**

Sensitivity analyses will be limited to the primary outcome and will consist of:

- An analysis is performed the same way as the primary analysis described in section 9.5 but now limited to the population that adhered to the allocated intervention as described in section 5.4.
- An analysis is performed to assess the effect of missing responses, in particular, the risk of bias they present. In the primary analysis described in section 9.5, all those recruited who have not reported variceal bleeding within 12 months are assumed to not have experienced the event. Here it is assumed that those who did not report variceal bleeding but have withdrawn, are lost to follow-up or have died within the 12-month follow-up period are missing the primary outcome response. Note that participants who are still actively in the trial at 12-months (are not withdrawn or lost to follow-up) but do not return the 12-month follow-up form will not be assumed missing.

Making these assumptions, firstly, an analysis is performed restricted to the population which has non-missing responses. Secondly, it is assumed that those with a missing response did not have variceal bleeding - the rationale being that the trial team would be

aware if bleeding had occurred due to the seriousness of the event and subsequent completion of an SAE form. Thirdly, the missing responses are assumed to be missing at random and are imputed via multiple imputation. In these three scenarios, the subsequent analysis performed is conducted in the same fashion as the primary analysis described in section 9.5.

- An analysis is performed on the primary analysis population in the same way as described in section 9.5 but with no covariate adjustment.

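### SAP sections 9.3, 9.4 and 9.10 disagree on which records define a variceal bleed, so a bleed recorded only on an SAE form may be coded as no bleed

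*SAP*

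**What the plan says.** Section 9.4, primary outcome, is the rule from which the variable is built. It says "Variceal bleeding events are identified on the 6 month and 12 month follow-up forms". It then says "Participants which do not fulfil this criteria for experiencing variceal bleeding will be termed" bleed-free. The answer is yes only if a bleed is flagged there and "the date of onset of the first episode of bleeding as indicated on the follow-up form is within 365 days" of randomisation. "Otherwise, it will be answered" no. The derivation of time to first bleed, also in 9.4, uses the same two forms and censors participants without a flagged bleed at the completion date of the latest trial form received.

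Two other sections describe the evidence differently:

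- Section 9.3: "a participant will be assumed to not have experienced variceal bleeding unless there is evidence to suggest otherwise". The kind of evidence is not named.
- Section 9.10: missing can be taken as no bleed because the trial team would be "aware if bleeding had occurred due to the seriousness of the event and subsequent completion of an SAE form".

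Elsewhere in 9.4 the SAE form is already a data source. "Deaths are identified on the SAE form", liver transplants are taken from the same form, and liver-related and cardiovascular deaths are classified after review of the SAE information.

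**The concern.** The SAP defends its no-bleed default by pointing to a form that its own derivation does not consult. Followed literally, 9.4 gives an SAE-recorded bleed no route into the primary endpoint unless a follow-up form also records it. The participants exposed are those who bleed and then leave the trial before the next form, and they include those whose bleed was fatal. Such a person could count as a liver-related death on the strength of the SAE information and as bleed-free in the primary analysis.

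At stake are the event rates, the power and, if loss differs by arm in this open-label trial, the risk ratio. There is also a question of reproducibility: one statistician following 9.4 and another following 9.3 and 9.10 could derive different primary outcomes from the same database.

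**Working it through.** **1. The passages side by side**

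| Section | Record that decides bleeding | If nothing is found there |
|---|---|---|
| 9.4, primary outcome | 6- and 12-month follow-up forms | coded no |
| 9.4, time to first bleed | the same two forms | censored |
| 9.3 | unspecified evidence | assumed no bleed |
| 9.10, rationale | SAE form | assumed no bleed |

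**2. Do the sensitivity analyses repair it?** Section 9.10 treats participants with no reported bleed who died, withdrew or were lost as missing. It then excludes them, codes them as no bleed, or imputes them as missing at random. The second option gives the same coding as the primary analysis. None of the three counts a bleed known from an SAE form as an event. The adherent-population and unadjusted analyses start from the same derived variable.

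**3. Reproducing the sample size (section 4.7)**

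Inputs: 12% and 8%, two-sided 5%, 90% power, 1:1 allocation.

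n per arm = [1.960·√(2p̄(1−p̄)) + 1.282·√(p₁(1−p₁)+p₂(1−p₂))]² / (p₁−p₂)²

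With p̄ = 0.10: [1.960·√0.18 + 1.282·√0.1792]² / 0.04² = (0.8315 + 0.5425)² / 0.0016, which rounds up to 1181 per arm, or 2362 in total. This matches the SAP. Inflation for 10% attrition gives 2362/0.9 = 2625 against the stated 2630. There is no arithmetic error.

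**4. Effect of lost bleeds**

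Sections 9.3 and 9.5 keep all randomised participants in the primary analysis with no missing outcome, so 1315 per arm is the relevant size. Let f be the share of bleeds not captured. The SAP does not give f. The upper value of 15% borrows the inpatient mortality for variceal bleeding in section 2 and assumes that no such death is followed by a follow-up form.

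Power = Φ{[(p₁−p₂)√n − 1.960·√(2p̄(1−p̄))] / √(p₁(1−p₁)+p₂(1−p₂))}, with each rate multiplied by (1−f).

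| f (both arms) | Banding / carvedilol | Bleeds lost per arm | Risk ratio | Power at 1315 |
|---|---|---|---|---|
| 0 | 12.0% / 8.0% | 0 / 0 | 0.667 | 92.8% |
| 5% | 11.4% / 7.6% | 7.9 / 5.3 | 0.667 | 91.4% |
| 10% | 10.8% / 7.2% | 15.8 / 10.5 | 0.667 | 89.8% |
| 15% | 10.2% / 6.8% | 23.7 / 15.8 | 0.667 | 87.9% |

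For f = 15%: (0.034·√1315 − 1.960·√0.15555) / √0.154972 = (1.2329 − 0.7730)/0.3937 = 1.168, and Φ(1.168) = 87.9%.

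**5. Unequal loss**

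Observed risk ratio = 0.08(1−f_carvedilol) / [0.12(1−f_banding)]. Two mirrored illustrations, neither taken from the SAP:

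- 15% lost in banding, 5% in carvedilol: 0.076/0.102 = 0.745.
- 5% lost in banding, 15% in carvedilol: 0.068/0.114 = 0.596.

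The true value is 0.667 in both, so the bias can go either way.

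**The case against.** The strongest reply is that sites may complete the follow-up form from the notes after a death or withdrawal. Section 5.4 has adherence transcribed from the medical notes onto the Follow-Up CRFs and, for those who leave early, based on information up to the point of exit. Appendix C takes physical examination, weight and blood tests from clinical records. If sites always do this, nothing is lost. The point stands as a possibility, but the SAP neither states nor requires it, and an earlier form could supply the same adherence data.

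A second reply is that 9.3 and 9.10 read together show an intention to count SAE-recorded bleeds. That is plausible. It supports changing 9.4, because 9.4 is the specific derivation and does not carry that intention.

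A reader might infer more than the SAP supports:

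- **That fatal bleeds are certainly removed from the endpoint.** This depends on form completion after exit, which is not described.
- **That power falls to 84.2%.** That figure applies 15% loss at 1181 per arm, whereas all 1315 are analysed. The 15% is itself a background figure for patients admitted with variceal bleeding, not a rate for this trial, whose endpoint also includes banding-related bleeds.
- **That the bias favours a particular arm.** The SAP gives no case fatality or form return by arm.
- **That 12-month forms completed early in the visit window add further loss.** That is a separate matter of visit timing, and sizing it would need assumptions about visit dates and hazard that the SAP does not supply.

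**Conclusion.** The three sections conflict on the definition of the primary event, and 9.4 as written omits the source on which 9.10 relies. That much is certain from the text. The consequence is conditional: an SAE-recorded bleed is miscoded only where no follow-up form recording it is completed after the participant dies, withdraws or is lost. Under that condition it becomes no bleed in the primary analysis and a censored observation in time to first bleed.

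The size cannot be determined from the SAP. With equal loss anywhere from 0 to 15%, the cost is at most about five points of power (92.8% to 87.9%) with no change in the risk ratio. Unequal loss would matter more, because it distorts the estimate itself. Since this is the primary endpoint and the data source is already in use for other outcomes, the sections should be reconciled before analysis.

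**What to change.** - **Section 9.4, both bleeding outcomes:** count a variceal bleed recorded on either follow-up form or on any SAE form, including a cause of death reported there, and take the earliest onset date. For the binary outcome, require onset within 365 days of randomisation.
- **Section 9.3:** name these records as the evidence that overrides the no-bleed assumption.
- **Section 9.10:** treat a participant as not having reported a bleed only if none of these sources shows one, so that known bleeds are not excluded, coded as no bleed or imputed.
- **Before database lock:** reconcile SAE and follow-up data on bleeding.

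The cost is SAP wording, a merge with SAE data and the reconciliation itself. The transplant derivation already reads an event category and an onset date from the SAE form, and cause of death is already reviewed. If the category does not separate variceal from other bleeding, the SAE descriptions would need a similar review. No new data need be collected from participants.

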#### **Secondary outcome measures**

##### *Time to first variceal bleed*

Variceal bleeding events are identified as adverse events on the 6 month and 12 month follow-up forms. If a participant has at least one episode of variceal bleeding (including banding-related bleeding) indicated on either of these follow-up forms then they have “experienced variceal bleeding”. Participants which do not fulfil this criteria for experiencing variceal bleeding will be termed “free from variceal bleeding”.

If a participant is termed as having “experienced variceal bleeding” then their time until bleeding will be defined as the number of days from the date of randomisation till the date of onset for the first variceal bleed occurring.

Participants who are termed as “free from variceal bleeding” and who were last known to be

bleeding-free prior to the 12-month follow-up time-point will be censored in the analysis. The time to censoring will be the number of days from the date of randomisation to the date last known to be free from variceal bleeding. This will be determined by the completion date of the most recent trial form received e.g. date of completion on the 12-month follow-up form. If the last known date in the trial is equal to the date of randomisation then the participant will be censored at day 1.

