## 4.7. Sample size

The sample size calculation has been based on published data from both a Cochrane meta-analysis of variceal banding versus beta-blockers and data from the first UK randomised trial of carvedilol published in this disease area. The Cochrane meta-analysis reported an overall 1-year variceal bleeding rate of 12% in the variceal banding ligation group. The 1-year bleeding rate was chosen for the primary outcome as Kaplan-Meier curves suggest that the majority of variceal bleeding occurs in the first year after treatment. In order to detect a 33% proportional difference in variceal bleeding rates (i.e. from 12% to 8%, a 4% absolute difference) between groups using a 2-sided test for comparison of proportions with a 1:1 allocation ratio, 90% power and a type I error rate of 5% (i.e.  $\alpha=0.05$ ), requires 2362 participants (1181 per group). Assuming and adjusting for a 10% attrition/loss to follow-up rate (based on the similar patient population studied), which is thus a conservative estimate due to our shorter duration of follow-up), increases the required sample size to 2630 participants in total (1315 per group).

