#### *Time To First Variceal Bleed*

Time to first variceal bleed will be compared between treatment groups using standard survival analysis methods. Kaplan-Meier survival curves will be constructed for visual presentation of time-to-event comparisons. Cox proportional hazard models will be fitted to obtain adjusted treatment effects which will be expressed as hazard ratios with 95% confidence intervals.

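### Time to first bleed is censored at a form-completion date, which can fall after death and leaves the 12-month case unfinished; separately, the Kaplan-Meier display does not treat death as a competing event

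*SAP*

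**What the plan says.** **Censoring rule (SAP 9.4, Time to first variceal bleed).** Bleed-free participants last known to be so before the 12-month time-point are censored at the last date they were known not to have bled. That date is then defined through paperwork: "This will be determined by the completion date of the most recent trial form received e.g. date of completion on the 12-month follow-up form". The section has no clause for death or transplant, and none for participants who are bleed-free at or after 12 months. Bleed times have no upper limit.

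**Source of deaths and transplants (SAP 9.4, All-cause mortality and Transplant free survival).** Both are identified on the SAE form. The dates of death and of transplant are derived there, but for other outcomes.

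**Analysis (SAP 9.6, Time To First Variceal Bleed).** "Kaplan-Meier survival curves will be constructed for visual presentation of time-to-event comparisons". Treatment effects are adjusted Cox hazard ratios. No competing-risk method is named, and section 9.10 limits sensitivity analyses to the primary outcome.

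**Primary outcome (SAP 9.3 and 9.4).** A bleed counts if its onset "is within 365 days of the date of randomisation"; every other participant is a no, including those who die without bleeding.

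**The concern.** There are two separate faults.

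1. **The censoring date.** A form reporting a death is completed after the death. If it is the last form received, the rule keeps the participant at risk of bleeding while dead. How long depends on how quickly a site completes its forms. The rule is also unfinished: it covers those last known bleed-free before 12 months, then offers the 12-month form as its example, and is silent on those who reach that point without bleeding. Two programmers could build different datasets from it.

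2. **The curve.** Even with deaths censored on the correct day, Kaplan-Meier treats death as if the participant could still bleed later. One minus Kaplan-Meier then estimates bleeding in a setting without death. The primary percentages count a bleed-free death as a no, so they behave like a cumulative incidence. The report would show two one-year bleeding figures per arm that disagree, with no explanation planned.

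At stake are the displayed curve and the clean interpretation of one secondary hazard ratio.

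**Working it through.** **Inputs from the SAP.** Section 4.7 gives an "overall 1-year variceal bleeding rate of 12% in the variceal banding ligation group" and a target "from 12% to 8%, a 4% absolute difference", with "90% power and a type I error rate of 5"%. The 12-month visit window is ±2 months (Appendix C), so it runs to about day 365 + 61 = 426.

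**Assumption.** The SAP gives no rate of death without bleeding in this population. The mortality figures in section 2 concern patients admitted with a variceal bleed. I take 5% to 20% at one year as a range.

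**Step 1: the plan's own figure.** Two proportions, pooled variance under the null:

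n = [1.960 × √(2 × 0.10 × 0.90) + 1.282 × √(0.12 × 0.88 + 0.08 × 0.92)]² / 0.04² ≈ 1,181 per group, or 2,362 in total.

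This matches section 4.7. The sample size is not in question; the step only confirms 12% and 8% as the planning values.

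**Step 2: deaths censored at the date of death.** Assume constant cause-specific hazards, one-year bleeding incidence b and death without bleeding m.

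- Total hazard: λ = −ln(1 − b − m)
- Bleeding hazard: λ_b = λ × b/(b + m)
- One minus Kaplan-Meier at one year: 1 − exp(−λ_b)

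Example with b = 0.12 and m = 0.10: λ = −ln(0.78) = 0.2485; λ_b = 0.2485 × 0.12/0.22 = 0.1355; 1 − exp(−0.1355) = 12.67%.

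| Death without bleeding (assumed) | 1 − KM, true 12% | Excess (points) | 1 − KM, true 8% | Excess (points) |
|---|---|---|---|---|
| 5% | 12.32% | 0.32 | 8.21% | 0.21 |
| 10% | 12.67% | 0.67 | 8.44% | 0.44 |
| 15% | 13.05% | 1.05 | 8.69% | 0.69 |
| 20% | 13.47% | 1.47 | 8.96% | 0.96 |

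A cumulative incidence estimate would return 12% and 8% in every row.

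**Step 3: the dead kept at risk for a lag D after death.** With S(t) the proportion alive and bleed-free and F_d(t) the proportion dead without bleeding, the risk set is R(t) = S(t) + F_d(t) − F_d(t − D). One minus Kaplan-Meier is 1 − exp(−∫ λ_b S/R dt). For b = 12% and m = 10%:

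| Lag (days) | 0 | 30 | 90 | 180 | 365 |
|---|---|---|---|---|---|
| 1 − KM | 12.67% | 12.57% | 12.38% | 12.17% | 12.00% |

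At a one-year lag nobody who dies leaves the risk set, so R = 1 − (bleeding incidence) and the estimate equals that incidence. Time counted after death therefore lowers the curve: it offsets the overstatement and does not cause it.

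**Step 4: the hazard ratio, deaths censored at death.** With equal deaths in both arms, the cause-specific ratio is 0.0857/0.1315 = 0.652 at 5% deaths and 0.649 at 20%. With deaths of 15% on banding and 10% on carvedilol it is 0.631; with the two reversed it is 0.671.

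**Step 5: no limit at day 365.** The curve at day 365 depends only on events and risk sets up to that day, so it does not change. Bleeds between days 366 and 426 would be Cox events but a primary no. At constant hazard and without deaths, incidence to day 426 is 1 − 0.88^(426/365) = 13.9% and 1 − 0.92^(426/365) = 9.3%, which is up to 1.9 and 1.3 points of extra events.

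**The case against.** **The rule aims at the last date known bleed-free, which cannot sensibly fall after death.** A careful programmer would probably stop at death. But the SAP says the form's completion date determines that date and makes no exception. That the SAE form is the last one received is an inference; it is plausible, not certain.

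**The curve is only a display and inference rests on Cox.** This limits the consequences. A cause-specific hazard ratio is a legitimate estimand and, with equal deaths, hardly moves. It has that meaning only if deaths are censored at the date of death, which the rule does not require.

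**A mortality imbalance would be visible anyway.** Mortality and transplant-free survival are reported by arm, so a reader could see it. That does not reconcile the two bleeding figures.

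**The missing one-year limit is consistent with the outcome definition.** This stands. Section 4.4 defines time to first bleed without a one-year limit, unlike mortality and transplant-free survival. A reader might infer that its absence is an error or biases the curve at day 365. Neither follows. What remains is the silence on those bleed-free at 12 months.

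**A large spurious difference between arms needs an extreme scenario.** This also stands. Equal 12% bleeding with 5% against 20% deaths gives a gap of about 1.1 points (13.465% minus 12.324%), but it assumes a 15-point mortality difference that nothing in the SAP suggests. Bleeding hazards among those alive would then truly differ, so the gap would not be pure artefact.

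**Conclusion.** The point holds as two distinct defects in one secondary outcome. First, the censoring rule, followed as written, can leave participants at risk after death and is incomplete for those bleed-free at or after 12 months. Second, the Kaplan-Meier display does not handle competing death. With deaths censored at death, it overstates one-year bleeding by about 0.3 to 1.5 points at a true 12% (0.2 to 1.0 at 8%), so it will not match the primary percentages.

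These sizes rest on constant hazards and on the assumed 5% to 20% death without bleeding. A lower rate shrinks them; any paperwork lag shrinks them further and unpredictably.

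Three stronger readings are not supported:

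- Follow-up past death does not cause the overstatement; it works in the opposite direction.
- The primary binary analysis is not compromised; it uses neither the censoring rule nor the curve.
- The SAP does not imply that transplant must be a censoring or competing event. That is a choice of estimand, which the SAP needs to state.

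**What to change.** In section 9.4, for time to first variceal bleed:

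- Censor at the earlier of the date of death and the last date on which bleed status was actually known (visit or notes date, not form completion).
- Give one rule for participants bleed-free at 12 months. Administrative censoring at day 365 is one option and would match the primary outcome's definition of a year.
- State how transplant is handled, with the reason.

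In section 9.6:

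- Show Aalen-Johansen cumulative incidence curves by arm, with death without bleeding as a competing event.
- Label the Cox result a cause-specific hazard ratio.

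The date of death is already derived for the mortality outcome, and the methods are standard. The cost is SAP wording and slightly more output. If the day-365 limit is adopted, later bleeds drop out of the Cox model, which loses a few events in exchange for agreement with the primary outcome.
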